### 6.2. CCC Participants

6-Month Supervised Exercise Intervention: The following exercise training protocols are within the accepted guidelines established by the American College of Sports Medicine [62]. The caregiver intervention group will have a 6-month supervised exercise program at the Medical Wellness Center three times weekly that will last 40–45 min. The activities will include resistance training (weightlifting) and endurance training (treadmill and bicycles). The study personnel at the center will oversee the training and testing of the caregivers and establish the exercise prescription. The participants will work with a coach who will direct the exercise performed and work intensity. At the end of each month, the investigators will retest the strength and adjust the weight lifted to match the change in strength due to the training effects. The resistance training protocol consists of seven exercises (chest press, seated row, shoulder press, pulldown, bicep curl, seated dip, and leg press), performed on selectorized resistance training equipment. During the first six weeks, the subjects will be asked to complete one set of 12–15 repetitions of each exercise. When 15 repetitions can be completed comfortably, without fatigue, and in good form, the resistance will be increased by 5–10%. This progression will continue each time the upper end of the repetition range is successfully completed. After six weeks, the repetition range will be adjusted to 8–12 repetitions per set and finally increased to two sets of 8–12 repetitions for weeks 13–72. The cardiovascular exercise prescription will range from 50 to 70% of the estimated VO_2_max for 20–40 min. VO_2_max will be estimated from the data collected during the submaximal treadmill protocol completed during the baseline fitness assessment (i.e., Bruce protocol). Initially, the subjects will start at 50% of the estimated VO_2_max for 20 min and systematically progress to 70% of the estimated VO_2_max for 40 min over the course of the three months. They will then maintain the latter intensity and duration for the remainder of their exercise training program.The 6-Month Nutritional Intervention will be carried out as described above for the SCI participants.The 6-Month Behavioral Intervention will be carried out as described above for the SCI participants.The 6-Month Self-care Extension-Phase Maintenance Program will be as described above for the SCI participants.

The Caregiver control group will follow a similar schedule but a different curriculum. Although they will have access to the same facilities (Medical Wellness Center) as the intervention group, the control caregiver participants will receive generic (“unstructured’) information about healthy eating and exercising without specific education on food types, exercise guidelines, caloric expenditure, or nutritional composition. The content sources will include online websites, such as *Web*MD Living Healthy (www.webmd.com/living-healthy, (accessed on 2 August 2016)), which typically provide generic information describing the need to exercise (but not providing an exercise prescription), eat well (but not providing a defined diet), and broad lifestyle recommendations. The study personnel at the Medical Wellness Center will oversee the testing of the caregivers without disability but will not establish any specific exercise prescription or training at any time of the intervention. The caregivers will be instructed by the Medical Wellness Center regarding the use of the facilities and safety guidelines.

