#### Eligibility Criteria

**Inclusion Criteria:**

**Criteria**

**Description**
Male and Female with SCI/D > 1 year, aged 18–65 years.Individuals of both sex with spinal cord injury/dysfunction (SCI/D) for more than one year, aged between 18 and 70 years.ASIA Impairment scale (AIS) A-C Spinal Cord Levels C5-L1Individuals with AIS scale ranging from A to D and spinal cord levels C5-L1Anyone or more of the following:Participants must meet at least one of the following criteria:a. Waist circumference >94 cm (37 inches)Waist circumference exceeding 94 cm (37 inches).b. BMI ≥ 22 kg/m^2^ [40,41]Body Mass Index (BMI) equal to or greater than 22 kg/m^2^.c. Fasting dyslipidemia (HDL-C≤ 40 mg/dL (male)/≤50 mg/dL (female), OR; TG ≥ 150 mg/dL)Presence of fasting dyslipidemia, indicated by HDL-C ≤ 40 mg/dL (males) or ≤50 mg/dL (females), or TG ≥ 150 mg/dL.d. Linked with caregivers: male and female 18–70 years who consent to co-enroll in the study as partnersCaregivers aged between 18 and 70 years, of both sex, who are willing to participate alongside the study participant and provide social and/or physical support. Caregivers include family members, significant others, or friends living with a disabled (SCI) partner and offering personal assistance, routine emotional encouragement, and/or social interaction.

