**Exclusion Criteria:**

For participants with SCI:
**Criteria****Description**Participating in at least 30 min of moderate-intensity physical activity for at least three months.Individuals engaged in moderate-intensity physical activity for a minimum of 30 min on at least three days per week for three months.Nutrition involving moderate caloric restriction for at least 6 months resulting in weight loss/gain ≥ 10% of total body massIndividuals who have undergone moderate caloric restriction resulting in a weight loss or gain of 10% of their total body mass over a period of at least 6 months.Surgery within 3 monthsIndividuals who have undergone surgery within the past three months.Grade 3–4 pressure ulcer within 3 monthsIndividuals who have had grade 3–4 pressure ulcers within the past three months.Limb pain that limits exerciseIndividuals experiencing limb pain that restricts their ability to exercise.Recurrent acute infection or illnessIndividuals with a history of recurrent acute infection or illness.PregnancyPregnant individuals.Previous myocardial infarction (MI) or cardiac surgeryIndividuals with a history of previous myocardial infarction (heart attack) or cardiac surgery.

For caregiver participants:
**Criteria****Description**Participating in at least 30 min of moderate-intensity physical activity for at least three months.Caregivers engaged in moderate-intensity physical activity for a minimum of 30 min on at least three days per week for three months.Nutrition involving moderate caloric restriction for at least 6 months resulting in weight loss/gain of 10% within the preceding 6 monthsCaregivers who have undergone moderate caloric restriction resulting in a weight loss or gain of 10% of their total body mass within the past six months.Surgery within 3 monthsCaregivers who have undergone surgery within the past three months.Limb pain that limits exerciseCaregivers experiencing limb pain that restricts their ability to exercise.PregnancyPregnant caregivers.Previous myocardial infarction (MI), cerebrovascular accident (CVA) or cardiac surgery that limits exerciseCaregivers with a history of previous myocardial infarction (heart attack), cerebrovascular accident (stroke), or cardiac surgery that limits their ability to exercise.Type I or II diabetes (by World Health Organization [WHO] criteria)Caregivers diagnosed with Type I or Type II diabetes according to World Health Organization (WHO) criteria.

Other exclusions applying to both groups:

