2.6-Month Nutritional Intervention: The nutritional intervention for the trial will consist of a 24-week energy-restricted Mediterranean-style diet. In accordance with the DPP study [74] and ADA guidelines [75], we will ensure that the participants have the daily energy consumption necessary to maintain baseline body weight and consider physical activity energy expenditure. The daily energy intake will be reduced to achieve a 500–1000 kcal/d deficit. This is sufficient to result in a weight loss of 1–2 lbs/week and approximately 7% of baseline body mass by the end of the 24-week intervention. The approximate target daily energy intakes prior to the adjustment for physical activity will be 1200 kcal/d for subjects weighing 120–170 lbs at baseline, 1500 kcal/d for subjects weighing 175–215 lbs at baseline, 1800 kcal/d for subjects weighing 220–245 lbs at baseline, and 2000 kcal/d for subjects weighing more than 250 lbs at baseline. The experimental nutrition will emphasize fruits, vegetables, whole grains, and olive oil, while animal sources of protein will be restricted to poultry and fish. The daily energy intake will be composed of 45–50% carbohydrate, 15% protein, and 35–40% fat. The daily fat intake will consist primarily of monounsaturated fats (18–20% of the daily energy intake) from olive oil (30–50 g/d, ~2.2–3.7 tbsp) and tree nuts (<20 g/d), with only a small portion from saturated fats (<7%) and the balance from polyunsaturated fats (10–13%). This macronutrient composition closely resembles those used by several recent investigations of Mediterranean-style nutrition [76,77,78]. While the relative carbohydrate consumption appears low (45–50% of daily energy intake), a lower-carbohydrate Mediterranean-style diet (<50%) results in greater body weight losses among obese women than higher-carbohydrate Mediterranean-style diets (>50%). In accordance with ADA guidelines, the intake of trans-fat will be minimized, the daily cholesterol intake will be limited to <200 mg/d, and the fiber intake will be targeted at 14 g/1000 kcal consumed.

A nutritional education and assessment will teach subjects food intake self-monitoring skills by using scales, measuring cups, and spoons provided to them for home use. Nutrition booklets will be provided, which will include information on common food items, food groups, servings, sample day-to-day menus, recipes, and food logs.

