3.6-Month Behavioral Intervention: general principles: The core DPP intervention will involve a generalized 16-session protocol aimed at altering behavior through education, problem-solving skills training, and cognitive restructuring (Table 3). The intervention will be delivered by a lifestyle coach assigned to the participant, primarily in a one-on-one format that allows tailoring of the intervention to the needs of the individual. To accommodate the specific demands of an SCI population, the general framework of the DPP training protocol will be replicated with modifications tailored to an SCI population. The complete curriculum is summarized in Table 3. The intervention structure consists of a total of 16 training sessions that cover various aspects such as education, nutrition, exercise, goal setting, and the self-monitoring of food intake and physical activity. The first eight sessions focus on providing information and strategies to address the psychological, social, and behavioral challenges associated with maintaining a behavior change. The remaining eight sessions concentrate on education, nutrition, exercise, outlining goals, and self-monitoring. Each training session will have an approximate duration of 30–60 min. To support the participants’ progress, each individual will receive a personalized lifestyle intervention manual. This manual will include their screening and pre-intervention assessment data, goals, key training elements, and motivational messages tailored to their specific needs. The manual serves as a valuable resource throughout the intervention, providing guidance and support to participants as they work towards their lifestyle change goals.

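### Every CCC caregiver is assigned the SCI weight-loss diet, yet caregivers need no weight or risk marker to enter and no lower BMI limit is set.

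*Protocol article*

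**What the plan says.** Section 6.2 (CCC Participants) defines the caregiver diet by reference alone: "The 6-Month Nutritional Intervention will be carried out as described above for the SCI participants". No condition on starting weight and no maintenance-energy version follows.

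The diet referred to is in section 6.1, nutritional intervention. Its core rule is "The daily energy intake will be reduced to achieve a 500–1000 kcal/d deficit", and the expected result is a loss of "approximately 7% of baseline body mass by the end of the 24-week intervention". Intake targets go by weight band, the lowest being: "The approximate target daily energy intakes prior to the adjustment for physical activity will be 1200 kcal/d for subjects weighing 120–170 lbs at baseline". No target is listed below 120 lb.

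Eligibility is in section 4.5. For people with SCI, "Participants must meet at least one of the following criteria": waist above 94 cm, BMI of at least 22, or fasting dyslipidemia. Caregivers qualify on age, willingness to co-enroll, and living with and supporting the partner. Their one weight-related exclusion is "moderate caloric restriction resulting in a weight loss or gain of 10% of their total body mass within the past six months". Also excluded are "Caregivers diagnosed with Type I or Type II diabetes according to World Health Organization (WHO) criteria" and, for both groups, people with pre-diabetes or recent use of glucose-lowering or lipid-altering drugs. Caregivers who already exercise regularly at moderate intensity are excluded too.

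Lower caregiver body mass is an intended effect (section 3, hypothesis II(a)).

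**The concern.** The diet was set up for a group selected for cardiometabolic risk and is then applied unchanged to a group that is not. The diabetes, pre-diabetes and drug exclusions remove some of the caregivers with most to gain from weight loss, and nothing removes those with no weight to lose. A lean caregiver can therefore enrol, be randomised to CCC and be prescribed a daily energy deficit together with supervised exercise three times a week.

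At stake is the safety of a small number of caregivers. Objective II concerns caregiver health and function, and the introduction stresses the physical demands of caregiving. An unneeded deficit in a lean caregiver does not serve that aim.

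**Working it through.** The article gives no figure to reproduce on this point. The check sets the eligibility text against the diet text and then sizes the consequence.

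**1. Could a risk marker be required of caregivers after all?** In the inclusion table the caregiver row is lettered d, in the same list as the waist, BMI and lipid items. If the list is read as one set of alternatives, item d alone satisfies it. If items a–c belong only to people with SCI, caregivers have no marker criterion. Neither reading requires a marker of caregivers.

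**2. Is there a BMI floor elsewhere?** The caregiver exclusions and the exclusions for both groups contain no low-weight or low-BMI limit.

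**3. Starting BMI that ends underweight.** Height is fixed, so BMI after a 7% loss = 0.93 × baseline BMI. The underweight limit is an assumption.

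| Assumed limit | Starting BMI below which the limit is crossed |
|---|---|
| 17.5 | 17.5 / 0.93 = 18.8 |
| 18.5 | 18.5 / 0.93 = 19.9 |
| 20 | 20 / 0.93 = 21.5 |

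Example: 125 lb (56.7 kg) at an assumed 170 cm is BMI 56.7 / 1.70² = 19.6. After the loss it is 0.93 × 19.6 = 18.2.

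**4. Who falls in the listed 1200 kcal/d band?** 120 lb is 54.43 kg, which equals BMI 19.89 at a height of √(54.43 / 19.89) = 1.654 m. The band therefore reaches caregivers below BMI 19.9 only from about 165 cm upward: roughly 120–127 lb at 170 cm, 120–134 lb at 175 cm and 120–142 lb at 180 cm. Shorter caregivers below BMI 19.9 weigh under 120 lb (at 160 cm, under about 112 lb). They have no listed intake, but the general deficit rule is not limited by weight.

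**5. How many people?** Section 4.5 plans 30 dyads with 20% attrition. An equal split gives 30 / 2 = 15 CCC caregivers, or 15 × 0.8 = 12 after attrition. The share starting below BMI 19.9 is not given, so a range is shown.

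| Assumed share | Of 15 | Of 12 |
|---|---|---|
| 5% | 0.8 | 0.6 |
| 10% | 1.5 | 1.2 |
| 20% | 3.0 | 2.4 |

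**6. Effect of a floor.** With a floor of 20, a caregiver just above it ends at 0.93 × 20 = 18.6. With a floor of 22, the end point is 0.93 × 22 = 20.5.

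**The case against.** The strongest reply is that a journal article condenses a fuller protocol, and individual diet exceptions may be written there or in an intervention manual. This stands as a reason for caution. It does not remove the point, because the article states both rules, eligibility criterion by criterion and the diet by explicit cross-reference, and the difficulty comes from applying them together.

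Second, there is oversight. Food logs go back weekly to study personnel (section 5.1, applied to caregivers in 5.2). Behavioral sessions use a "one-on-one format that allows tailoring of the intervention to the needs of the individual". Each site has a trial physician and the trial an independent medical monitor (section 7). Table 1 schedules caregiver weights at months 2, 4 and 6. These measures make unnoticed progression less likely. None waives the deficit, and because weight loss is the intended effect, it need not prompt review. The mention in section 6.1 of the energy needed to hold baseline weight describes the level from which the deficit is subtracted.

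Third, excluding already active caregivers plausibly removes some of the leaner ones. This may lower the affected share by an unknown amount.

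Fourth, the gap is not peculiar to caregivers. An SCI participant who enters on waist or lipids alone also has no BMI floor. That is correct, and the fix covers it.

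A reader might go further in two directions that the article does not support. One is to multiply 1–2 lb/week by 24 weeks and conclude that a 120 lb caregiver would lose 24–48 lb (20–40%). The article states the 24-week result as about 7%, so that is the figure used here. The other is to treat the caregiver comparison as biased. Allocation is random and the diet is part of the CCC package, so it is not.

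**Conclusion.** The point holds as a limited safety matter. As written, all CCC caregivers receive the energy deficit, caregiver eligibility asks for no weight or risk marker, and no lower BMI limit exists. A caregiver starting below about BMI 19.9 would end underweight if the target is met.

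This size rests on three assumptions: 18.5 as the underweight limit (17.5 to 20 moves the threshold from 18.8 to 21.5), full achievement of the 7% loss, and an assumed share of lean caregivers. On the shares shown, about 1 to 3 of 15 people are concerned. The true number is unknown, probably small, and may be lower still given the oversight and the activity exclusion.

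The caregiver diet rule does not touch the primary outcome, body mass in the SCI group. It would be wrong to infer that BMI 22 is a floor protecting SCI participants, since it is one of several alternative criteria.

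**What to change.** In section 6.2, state that CCC caregivers below a pre-set low baseline BMI (for example 20, and no higher than the protocol's own 22) receive the same Mediterranean-style composition at maintenance energy, with the full exercise and behavioral programme. In section 6.1, apply a floor in the same way to SCI participants who enter without the BMI criterion, at a cut-off the study physicians judge suitable for SCI. Keep all randomised caregivers in the hypothesis II(a) comparison, and describe body-mass change by baseline BMI.

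The cost is a sentence in each section and one descriptive table. Weight is already measured at months −2 and 0, before the diet starts, so no new data are needed.

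The expected mean loss in the CCC arm shrinks slightly. If exempt caregivers lose nothing and the rest reach 7%, exempting 10% gives 7 × 0.9 = 6.3%, and exempting 20% gives 7 × 0.8 = 5.6%. Keeping the cut-off low limits this dilution. The few exempt caregivers would also have a different energy prescription from their partners. On the SCI side, one exempt participant among 24 completers (30 × 0.8) would lower the planned mean loss to 7 × 23/24 = 6.7%.

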## 7. Trial Safety and Adverse Events

Each trial site will have an assigned medical director to serve as the trial physician and oversee all aspects of participant medical care. The trial will also have an assigned independent medical monitor providing trial medical oversight and project evaluation plans. All testing will be performed at a medical center that is located near an emergency room, and all facilities and trial personnel are trained on the standing policies and procedures for emergencies. This will be designed to reduce the risks and burdens, with the further aim of reducing the potential risks and burdens through strict adherence to best practices [79].

Any adverse events or serious adverse events that occur during the study will be promptly reported to the Institutional Review Board (IRB) within the required timeframe. In the event of an adverse event, the principal investigator will immediately inform and seek advice from the study physician. The study physician will assess whether the event(s) can be attributed to the study procedures outlined in the protocol. The evaluation of adverse events by the study physician will be conducted using the following criteria [80]:i.Grade 1 (mild): Individuals experience an awareness of symptoms, which can be easily tolerated. These symptoms are typically transient and do not necessitate any specific treatment. They do not interfere with the individual’s usual or normal daily activities.ii.Grade 2 (moderate): Symptoms may be improved with simple therapeutic measures. While they may interfere with the individual’s normal daily activities, they do not prevent them from participating in these activities.iii.Grade 3: This level of adverse event represents an incapacitating event where the individual experiences an inability to perform their usual activities.iv.Grade 4 (life-threatening/disabling): In this category, the participant is in a critical condition where there is a risk of death, worsening disability, or impairment compared to their pre-existing condition at the time of the event.

For adverse events categorized as grades 1 and 2, the investigators will closely monitor the participant and provide standard medical or therapeutic care as needed. If there are repeated instances of grade 1 and 2 events, the investigators may deem it necessary to notify the Institutional Review Board (IRB) and consider halting the study. In such cases, the investigators will take the appropriate action and inform the IRB accordingly. For grade 3 and 4 events, each occurrence will be individually assessed. If any grade 3 or 4 event takes place, it may prompt the investigators to notify the IRB and consider stopping the study. The investigators will follow the necessary steps and inform the IRB accordingly. In the absence of such circumstances, if the IRB determines that the serious adverse event is related to the protocol, the study will be halted and undergo evaluation to determine if it should continue.

## 8. Data Management

### 8.1. Electronic Data Records

All electronic files will be stored on password-protected computer terminals located in the Christine E. Lynn Rehabilitation Center for the Miami Project to Cure Paralysis, the University of Miami Miller School of Medicine, and Craig Hospital. Computer security is provided through data encryption, firewall protection, and data backup on the Miami Project server, accompanied by a DUO Multifactor Authorization. All source data obtained will be entered into a de-identified data bank and stored securely on the network.

### 8.2. Physical Data Records

Data will be stored in a locked filing cabinet, within a locked room, and behind two levels of access security at the Christine E. Lynn Rehabilitation Center and Craig Hospital. The source data from the laboratory and testing equipment are kept under the same level of access security described above.

